We do not share the opinion of Reviewer #1 that virologic failure is of little consequence. Most experts would agree that it is not advisable to allow persons on ARVs to experience virologic failure. Individuals who acquire HIV-1 infection in 2008 are predicted to live for decades following infection, much of the time while receiving ARV therapy. Although several highly effective agents from different ARV classes were recently approved, the rapid development, for example, of the M184V mutation completely eliminates the ability to construct a standard-of-care ARV regimen that is once-a-day and easily tolerated. Increasing pill burden, dosing frequency, and/or increased medication side effects from subsequent regimens would reduce adherence and the chance of virologic success. Thus the initial virologic failure is not without long-term consequences, whether it is in acute or established HIV-1 infection.

2. "The partner studies proposed … addresses an important area of research, but the number of subjects studied to [date] is small and it is still unclear whether [there will be] an adequate number of subjects to adequately power the studies."

In **5.c.3** we explain in detail how the combination of our recruitment record, the likelihood of confirming putative partners, and the likelihood that source partners would have HIV-1 drug resistance will achieve a sample size that has adequate power for the proposed analyses. "… we will have 82% power to detect a transmission probability of all source partner mutations of 80% or less if we have 17 confirmed partner-pairs in which the source partner has at least one HIV-1 drug resistance mutation…" We would need to enroll 0-21 putative source partners in order to have a total of 17 confirmed partner-pairs in which the source partner has at least one drug resistance mutation. Notably, three partner-pairs have enrolled in the last six months. With continued enrollment, we will have enrolled the maximum number of needed partner-pairs by the end of year five.

3. re: Aim 1: "It is unclear how the determination that low-frequency mutations are rapidly lost to detection would support drug resistance testing at the time of entry into care."

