Compared to consensus sequencing, OLA identified more subjects with transmitted resistance in both plasma (**4a**, p<.0001, by McNemar's exact test) and PBMCs (**4b**, p=.001). There was not a significant difference in the number of subjects with mutations detected by OLA in plasma and PBMCs (**4d,** p=.3).

***Table 5*** *shows the specific mutations that were detected. No subject had the L74V (NRTI) or D30N (PI) mutations. Four subjects had one HIV-1 drug resistance mutation detected by both consensus sequencing and OLA (one with M184V, two with G190A, and one with L90M). The subject with L90M and two other subjects had intermediate genotypes between wild-type and mutant (T215Q and T215D) that were detected by consensus sequencing; screening for T215F and T215Y by OLA yielded indeterminate results. With the use of OLA, the detection of NRTI resistance increased from 4% to 17% of subjects, the detection of NNRTI resistance increased from 2% to 9% of subjects, the detection of PI resistance increased from 1% to 19% of subjects, and the detection of multi-drug resistant HIV-1 increased from 1% to 9% of subjects. Overall, 34% (95% CI 25-44%) of subjects had transmitted HIV-1 drug resistance. These data show our ability to use OLA to identify transmitted low-frequency HIV-1 drug resistance and demonstrate a high prevalence of drug resistance that was not detected by consensus sequencing in our cohort of subjects with primary HIV-1 infection.*

Table 5: Number of subjects with HIV-1 drug resistance mutations detected by OLA in PBMCs, plasma, or both, by mutation

|  | *NRTI* | | | | *NNRTI* | | | *PI* | | | | |
| --- | --- | --- | --- | --- | --- | --- | --- | --- | --- | --- | --- | --- |
|  | *K65R* | *K70R* | *M184V* | *T215F/Y* | *K103N* | *Y181C* | *G190A* | *I50V* | *V82A/S/T* | *I84V* | *N88D* | *L90M* |
| *PBMCs only* | *4* | *2* | *5* | *5* | *2* | *-* | *1* | *1* | *1* | *-* | *4* | *-* |
| *Plasma only* | *2* | *1* | *2* | *3* | *-* | *4* | *-* | *7* | *-* | *2* | *3* | *-* |
| *Both* | *2* | *-* | *-* | *-* | *-* | *-* | *2* | *-* | *1* | *2* | *-* | *1* |

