Analysis for the primary objective will be calculated as a binomial probability of the number of mutations transmitted from each source partner to the recipient partner, conditional on the number of mutations in the source partner. This accounts for the fact that source partners will undoubtedly have different numbers of HIV-1 drug resistance mutations. For the purpose of sample size calculations, we assume that the number of mutations in the source partners follows a Poisson distribution with the expected number of mutations being two. Power calculations are based on simulations, repeated 1000 times. Each simulation estimates the binomial probability of transmitting a mutation conditional on the number of mutations in the source partners, and calculates the associated 95% confidence intervals based on normal approximation for the estimated probability. The type II error is calculated as the number of simulation replicates where the 95% confidence interval contains the value of 1, when the simulated transmission probability is less than 1.

Using the simulation analyses described above, we will have 82% power to detect a transmission probability of all source partner mutations of 80% or less if we have 17 confirmed partner-pairs in which the source partner has at least one HIV-1 drug resistance mutation. *Overall, the subset of recipient partners who had resistance identified by OLA (4/12=33%) was similar to the population studied in the pilot project. Of the 18 confirmed partner pairs without complete OLA testing, we would expect 6 to 18 source partners to have HIV-1 drug resistance. Based on our prior experience with confirming putative source partners, we would expect that the relationship of 14 of the remaining 17 partner-pairs would be confirmed, and 5 to 17 of these source partners would have HIV-1 drug resistance. We would therefore need to enroll at most 21 (and likely fewer) new putative source partners in order to have at least 6 additional confirmed source partners with HIV-1 drug resistance.*

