**5.g Timetable for all projects**

Y1 0-6 months Submission of modification to IRB application

Confirmation of yet-to-be confirmed transmission pairs in PIC Partner Study

Continued enrollment in PIC Cohort and PIC Partners Studies (through Y5)

Y1-2 OLA of source and recipient partner-pairs (Aim #3)

Y2-3 OLA of untreated subjects (Aim #1)

Data analysis and manuscript preparation of Aim #3

Y3-4 OLA of treated subjects (Aim #2)

Data analysis and manuscript preparation of Aim #1

Y4-Y5 Data analysis, manuscript preparation of Aim #2 and future grant submission

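### Aim 3 recruitment: the figure of at most 21 new source partners is a rounded expected need at the lowest resistance prevalence considered, not a maximum; separately, the range of 5 to 17 resistant sources among 14 confirmed pairs is impossible

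*Protocol*

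**What the plan says.** Section 5.c.3 of the protocol claims "82% power to detect a transmission probability of all source partner mutations of 80% or less if we have 17 confirmed partner-pairs". A pair counts only when its source carries one or more resistance mutations. The section then projects how many such pairs will be available.

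- **Prevalence.** The low end comes from recipient partners: "the subset of recipient partners who had resistance identified by OLA (4/12=33%) was similar to the population studied in the pilot project". The pilot result in section 4.g is "Overall, 34% (95% CI 25-44%) of subjects had transmitted HIV-1 drug resistance".
- **Pairs already confirmed.** "Of the 18 confirmed partner pairs without complete OLA testing, we would expect 6 to 18 source partners to have HIV-1 drug resistance".
- **Pairs pending.** Of 17 pending pairs, 14 are expected to be confirmed, and "5 to 17 of these source partners would have HIV-1 drug resistance".
- **New partners.** "We would therefore need to enroll at most 21 (and likely fewer) new putative source partners", to supply at least 6 further qualifying sources.

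Section 1, in the response to Critique #1 (item 2), repeats the figure as a range: "We would need to enroll 0-21 putative source partners in order to have a total of 17 confirmed partner-pairs". It adds that three partner-pairs enrolled in the last six months and that the largest number needed will be enrolled by the end of year five. The timetable in 5.g continues enrolment through year 5 but gives one testing entry for this aim: "Y1-2 OLA of source and recipient partner-pairs (Aim #3"). Analysis and manuscript follow in years 2-3.

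**The concern.** There are two separate faults and one mismatch.

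First, the range for the pending pairs refers to the 14 expected to be confirmed, so its upper end cannot exceed 14. The 17 is the count before confirmation.

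Second, the recruitment need is presented as a ceiling, but each step multiplies point estimates. A ceiling should hold in the worst case considered. Here the calculation gives only the average outcome in that case, with no allowance for chance.

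Third, the timetable has no Aim 3 testing after year 2, although section 1 relies on accrual to year 5.

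The number matters because section 1 uses it to answer a criticism that Aim 3 might not have enough pairs. If 17 qualifying pairs are not reached, the stated 82% power does not apply.

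**Working it through.** **Inputs (5.c.3 unless noted).** Target T = 17 qualifying pairs. Low-end prevalence p = 4/12 = 1/3, or 34% from the pilot (4.g). Confirmed pairs without complete testing: 18. Pending pairs: 17, with confirmation rate c = 14/17 = 0.8235. An alternative confirmation rate is 10/11, from the early partner analysis in 4.h.

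**Reproducing 21.**
- Confirmed pairs: 18 × 1/3 = 6.
- Pending pairs: 14 × 1/3 = 4.67, rounded up to 5.
- Still needed: 17 − 6 − 5 = 6.
- New partners: 6/(p·c) = 6/(0.34 × 0.8235) = 21.4, or 6/(0.3333 × 0.8235) = 21.9.

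So 21 is an expected-value result, rounded down. It uses the lower end, 5, and not the 17 at the upper end. The 0 in the section 1 range does not depend on the 17 either: at 100% prevalence the 18 confirmed pairs already exceed the target.

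**What 21 partners yield on average.** At p = 1/3, 21 × 0.8235 × 0.3333 = 5.76, below the 6 required. The total is 6 + 4.67 + 5.76 = 16.4. At 34% the total is 6.12 + 4.76 + 5.88 = 16.8. Without rounding 4.67 up to 5, the expected need is (17 − 32p)/(p·c), where 32 = 18 + 14. This gives 23.1 at 1/3 and 21.9 at 34%.

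**Chance of reaching 17.** Let the total be Bin(18, p) + Bin(17, p·c) + Bin(21, p·c), computed by exact convolution:

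| Source prevalence p | Expected total | P(total ≥ 17) |
|---|---|---|
| 25% (lower limit of the pilot CI) | 12.3 | 0.09 |
| 1/3 | 16.4 | 0.48 |
| 34% | 16.8 | 0.52 |
| 40% | 19.7 | 0.82 |
| 50% | 24.6 | 0.99 |

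**Sensitivity at p = 1/3.** The protocol reports 19 confirmed pairs, of which the projection counts 18; the result for the other pair is not in the text available. Counting it as one more random pair gives 0.52. Assuming its source is resistant gives 0.60. Keeping 18 pairs but using a confirmation rate of 10/11 gives 0.61.

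**Number needed for a stated assurance.** The smallest n of new partners with P(total ≥ 17) of at least 0.80 is 33 at p = 1/3 and 32 at 34%. For 0.90 it is 40 and 38.

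**Likely accrual.** Three pairs in six months, if sustained (an assumption), is six a year, or about 30 in five years. With n = 30, P(total ≥ 17) is 0.74 at 1/3, 0.77 at 34% and 0.95 at 40%.

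**The case against.** The strongest reply is that 21 belongs to the bottom of a scenario range running from 33% to 100% resistance among sources, and that the sentence itself says fewer will probably be needed. The 33% was seen in recipients, and the Aim 3 hypothesis is that resistance is less common in recipients than in sources, so the protocol has a reason to treat 33% as a low value. This stands: the near-even chance applies only at 33-34% and should not be quoted without that condition. It does not rescue the word maximum, because at the end of the range that produced 21 the average outcome already falls short. Nor is 33% a firm floor, since the pilot's own interval goes down to 25%.

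It is also fair that planning on expected counts is common in grant applications, and that 21 is a projected need rather than an enrolment cap. Contact with all eligible partners will be attempted, and enrolment continues through year 5. At the recent pace about 30 partners would accrue, so the prospect for the study as planned is better than the figure at 21. That argues for restating the number; it does not make 21 an upper bound.

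Two stronger readings are tempting. A reader might infer that 21 was derived from the impossible 17; the arithmetic shows that it was not. A reader might also infer from 5.g that partners enrolled in years 3-5 would never be tested. The protocol does not say so. Its response to Critique #3 in section 1 calls the results of the first two years preliminary and says the added sample size for all aims needs the longer enrolment. Section 5.a plans continued enrolment of pairs, and 5.c.3 plans testing of confirmed source partners. What can be said is that 5.g schedules no later Aim 3 testing or final analysis.

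**Conclusion.** The point holds in a limited form. The upper end of 17 among 14 confirmed pairs is a plain error with no effect on the recruitment figure. Calling 21 a maximum is wrong: it is the rounded expected need at 33-34% source prevalence. There it gives about 16.4-16.8 qualifying pairs on average and reaches 17 with probability about 0.48-0.52, or 0.52-0.61 at 1/3 under the alternative inputs. At 40% or more the same 21 partners are likely to suffice.

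These results assume independent pairs, one common prevalence among sources, and confirmation unrelated to resistance. The 17-pair target and its 82% power are taken as stated and were not examined here. No analysis method or enrolment rule is affected. What needs correcting is a recruitment assurance and a timetable that does not show the later testing it depends on.

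**What to change.** 1. In 5.c.3, change the range for the pending pairs to 5 to 14.
2. In 5.c.3 and in the section 1 response, replace the ceiling of 21, the range 0-21 and the reference to a maximum number of pairs. Give instead the expected need at the low-end prevalence (about 22-23 new partners) and the number giving 80% assurance there (about 32-33). State the prevalence and confirmation rate used, and note that fewer are needed if source prevalence is higher.
3. Set this against expected accrual: about 30 partners in five years if the recent pace holds, with a chance of about 0.74-0.77 of reaching 17 at 33-34%.
4. In 5.g, add a later Aim 3 testing batch and a final Aim 3 analysis after the later enrolment, and label the early results as preliminary, as section 1 already does.

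The cost is a few restated numbers and timetable lines. The recruitment need will look somewhat less favourable, and the final Aim 3 analysis moves later than the current timetable shows.

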To further explore which specific mutations are more likely to be transmitted and result in subsequent HIV-1 infection, we will conduct a logistic regression analysis with generalized estimating equations to account for correlation of the presence of different mutations within the same source partner. In this analysis, each individual mutation will be evaluated, with the outcome in the regression model; transmitted to partner Yes/No. Indicator covariates will be used to identify specific mutations. To account for the potential loss of detection of mutants over time, an exploratory analysis will adjust for the estimated time between the transmission event and the dates samples are obtained from the transmission pair for HIV-1 drug resistance testing.

We will also use the semi-quantitative nature of OLA to categorize HIV-1 drug resistance mutations as comprising <5%, 5-10%, 10-30%, 30-50%, and 50-100% of the viral quasi-species. We will compare the level of specific HIV-1 drug resistance mutations in the source and recipient partners to identify, for example, whether a mutation exists as 5-10% of the population in the source partner but 10-50% in the recipient. Analyses will control for HIV-1 RNA levels at the time of HIV-1 transmission.

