**Figure 8: Examples of results of OLA testing for M184V**

**Figure 8:** Examples of optical densities (ODs) from negative controls; 2%, 5%, and 100% dilutions of cloned mutant virus; and subject samples are shown. All samples are tested in duplicate. A sample is identified as mutant (grey bar) if the mean OD for the two samples at 490nm is greater than the OD for the 5% mutant. This threshold is indicated by the horizontal line. If this requirement is met, but the OD is less than 0.2, the sample is re-tested. If the re-tested sample is again greater than the OD for the 5% mutant, a mutant variant is presumed present. 95% confidence intervals for ODs are indicated by vertical hash marks.

The mutations to be tested include K65R, K70R, L74V, M184V, T215F/Y (NRTI resistance); K103N, Y181C, and G190A (NNRTI resistance); and D30N, I50V, V82S/A/T, I84V, N88D, and L90M (PI resistance). For the semi-quantitative assays, comparisons will include 2%, 5%, 10%, 30% and 50% dilutions of known mutant virus after DNA viral quantification (**Figure 8**). For quality control purposes, duplicates of test specimens and all controls [water (negative control), mutant (positive control), and wild-type (positive control)] are run on the same plate. Biannual verification of the assay is performed using blinded specimens previously identified by consensus sequencing.

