**5.f.4 Power**

As previously mentioned, this study has limited power for the analysis comparing the time to virologic failure among subjects with and without transmitted HIV-1 drug resistance who initiate ARV therapy. We will instead perform an analysis comparing the time to virologic suppression, which has been used as a surrogate outcome by other seminal studies that evaluated the impact of transmitted drug resistance on the response to ARV treatment [52, 53, 56, 190]. In addition, the time to virologic suppression and other markers of early treatment response have been associated with longer-term treatment outcomes [191-193]. If our results suggest that transmitted low-frequency HIV-1 drug resistance has an adverse impact on response to ARV therapy, a randomized clinical trial will be designed to definitively answer these questions.

These studies will also not have sufficient power to identify specific mutations that may be particularly clinically relevant (e.g. K103N) because of the infrequent transmission of any one particular HIV-1 drug resistance mutation and the frequent co-transmission of mutations. Similarly, we will not be able to determine if there are differences in the rate of loss of detection or compare rates of transmission between specific mutations.

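### Aim #3's exploratory GEE with mutation indicators would give at least one infinite odds ratio in nearly every dataset, for a comparison that 5.f.4 says cannot be made

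*Protocol*

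**What the plan says.** Aim #3 has one primary objective, the overall probability that a source partner's mutations are transmitted. Its first secondary objective (Protocol 5.b) is to explore whether that probability differs between specific mutations.

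For that secondary objective, 5.c.3 plans a "logistic regression analysis with generalized estimating equations to account for correlation of the presence of different mutations within the same source partner". Each mutation in a source partner is one record, and the outcome is transmitted, yes or no. On the covariates it says "Indicator covariates will be used to identify specific mutations". An exploratory version adjusts for the time between transmission and sampling. The section gives no minimum count per mutation, no grouping and no method for sparse data.

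The sample size in the same section is set for the primary objective. It claims "82% power to detect a transmission probability of all source partner mutations of 80% or less" with "17 confirmed partner-pairs in which the source partner has at least one HIV-1 drug resistance mutation", and for this "we assume that the number of mutations in the source partners follows a Poisson distribution with the expected number of mutations being two".

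Section 5.f.4 (Power) then lists, among the things the study will not be able to do, to "compare rates of transmission between specific mutations".

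**The concern.** There are two linked problems. First, 5.b and 5.c.3 plan a comparison that 5.f.4 says the study cannot make. Second, 5.f.4 presents the limit as one of power. Low power gives wide but finite intervals. Here many mutations would be carried by only a few source partners, and such a mutation is easily transmitted in all of its carriers or in none. Its log-odds then has no finite estimate (separation), and the sandwich standard error for that level has no useful meaning.

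The reported odds ratio for such a mutation depends on where the software stops iterating. If the reference mutation is itself separated, every contrast against it is infinite. A ranking of mutations by transmissibility read from this output would partly reflect which mutations happened to be rare.

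**Working it through.** **Inputs from the Protocol**
- 5.c.3: 17 pairs with at least one source mutation; Poisson mean 2; transmission probability 0.80.
- 5.e.5: the panel has 14 entries when T215F/Y and V82S/A/T are each counted once. Section 5.a speaks of 17 codons.
- Table 5 (pilot): totals over the 12 mutations seen are K65R 8, K70R 3, M184V 7, T215F/Y 8, K103N 2, Y181C 4, G190A 3, I50V 8, V82A/S/T 2, I84V 4, N88D 7, L90M 1; sum 57.

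**Assumption.** The Table 5 frequencies come from newly infected subjects, not source partners. They are used here as a stand-in, with a check that replaces them by equal frequencies.

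**The plan's own figure.** The 82% power uses an interval described as "calculates the associated 95% confidence intervals based on normal approximation for the estimated probability" and counts a success when that interval excludes 1. Simulation gives 82.0% when the per-pair proportions are averaged and sources drawn with no mutation are dropped. Other readings give 57% to 96%. So the planning values are usable as stated. No power or size is stated for the mutation-specific model.

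**Expected counts at 17 pairs**
- Mean mutations per source, given at least one: 2 / (1 − e⁻²) = 2.313.
- Records: 17 × 2.313 = 39.3.
- Non-transmissions at 80%: 0.20 × 39.3 = 7.9 (simulated 95% range 3 to 14).

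**Why levels separate.** A mutation with n independent records is separated with probability pⁿ + (1 − p)ⁿ. At p = 0.80:
- n = 1: certain.
- n = 2: 0.64 + 0.04 = 0.68.
- n = 3: 0.512 + 0.008 = 0.52.
- n = 5: 0.328 + 0.0003 = 0.33.

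About 10.9 mutations appear per dataset, so the average is 39.3 / 10.9 = 3.6 records per mutation.

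**Simulated separation.** Mutations were drawn without replacement within a source, at the Table 5 frequencies.

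| Pairs | Transmission | Non-transmissions | Levels present | Levels separated | Datasets with at least one separated level |
|---|---|---|---|---|---|
| 17 | 80% | 7.9 | 10.9 | 5.8 | over 99.9% |
| 17 | 65% | 14 | 10.8 | 4.1 | 99.6% |
| 17 | 50% | 20 | 10.8 | 3.7 | 99% |

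With 14 equally likely mutations, 17 pairs and 80%, about 13.3 appear and 7.8 are separated. Logistic GEE fits with an independence working correlation were also run: 150 of 150 had a non-finite coefficient or one above 10 in absolute size.

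**More pairs.** Section 5.c.3 counts 18 confirmed pairs without complete OLA testing and expects 14 more to be confirmed. If every source were resistant, that gives 18 + 14 = 32 pairs, or 32 × 2.313 = 74 records and 0.20 × 74 = 14.8 non-transmissions at 80%. At least one level is still separated in about 99.5% of datasets at 80%, 95% at 65% and 90% at 50%.

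**Drug class instead of mutation.** With three indicators (NRTI, NNRTI, PI) and 17 pairs, a separated level occurs in about 31% of datasets at 80%, 10% at 65% and 6% at 50%.

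**Time since transmission.** When a pair-level time covariate with no true effect was added to the full-indicator model, its coefficient and standard error were finite in 98.5% of fits at 17 pairs and 80%, and in 99.5% to 100% at 65% and 50%.

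**The case against.** The strongest reply is that this is a secondary analysis labelled exploratory, and that 5.f.4 already concedes there is too little information on specific mutations. Section 5.c.3 also does not say that every panel mutation enters one model; a minimum count or a grouping could be set in a SAP, which is not at hand. All of this limits the weight of the point. It does not remove it: 5.c.3 evaluates each individual mutation, so one indicator per mutation is the natural reading, and a statement that the comparison cannot be made conflicts with a model that makes it.

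A reader might infer more than the documents support:
- **That the model cannot be estimated at all.** Separation is local to a level. At 17 pairs and 80%, about 5 of the 11 mutations present keep finite, though very imprecise, estimates.
- **That the time adjustment fails too.** The refits above show that it generally does not.
- **That there are more coefficients than non-transmissions, or that most mutations separate.** This holds mainly at 17 pairs and 80%. The first occurs in 82% of datasets there but 16% at 65%; the second in 52% and 14%. Seventeen is a minimum target, and the power statement covers 80% or less.

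It is also fair to object that Table 5 does not describe source partners. The check with equal frequencies leads to the same conclusion.

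**Conclusion.** The point stands as a defect in a secondary analysis. The mutation-indicator model in 5.c.3 would return at least one infinite odds ratio in over 99% of datasets at the planning values, in about 99% at 50% transmission with 17 pairs, and in about 90% to 99.5% with 32 pairs. Around half of the mutation levels present are affected at 17 pairs and 80%; the standard errors for those levels are unusable. Sections 5.b and 5.c.3 also disagree with 5.f.4 on whether the comparison can be made.

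This rests on one indicator per mutation, Poisson mean 2 given at least one, independent transmission of mutations, and pilot frequencies carried over to source partners. The figures of 39 records and 8 non-transmissions are derived from the planning values and are not stated in the Protocol. The primary objective of Aim #3 and its sample size do not depend on this model.

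**What to change.** In 5.c.3, replace the mutation-indicator model by a description: for each mutation, the number transmitted over the number present in source partners, with an exact interval and no test between mutations. Word the secondary objective in 5.b to match, so that both agree with 5.f.4.

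If a regression is kept as exploratory, use drug class (NRTI, NNRTI, PI) in place of the mutation indicators. Fit it with a method that tolerates separation, for example a Firth-type penalty, and correct the variance for about 17 clusters. The penalty is still needed because class indicators separate in about 30% of datasets at 17 pairs and 80%. Time since transmission can stay as an added covariate.

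The change affects the analysis text only and needs no new data. The cost is mutation-level odds ratios, which these data could not support. Drug class also answers a coarser question than the one in 5.b, and the text should say so.
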